## Abstract

**Introduction:**

Many types of prostate cancer present minimal risk to a man’s lifespan or well-being, but existing terminology makes it difficult for men to distinguish these from high-risk prostate cancers. This study aims to explore whether using an alternative label for low-risk prostate cancer influences management choice and anxiety levels among Australian men and their partners.

**Methods and analysis:**

We will run two separate studies for Australian men and Australian women with a male partner. Both studies are between-subjects factorial (3×2) randomised online hypothetical experiments. Following consent, eligible participants will be randomised 1:1:1 to three labels: ‘low-risk prostate cancer, Gleason Group 1’, ‘low-risk prostate neoplasm’ or ‘low-risk prostate lesion’. Participants will then undergo a second randomisation step with 1:1 allocation to the provision of detailed information on the benefits and harms of different management choices versus the provision of less detailed information about management choices. The required sample sizes are 1290 men and 1410 women. The primary outcome is the participant choice of their preferred management strategy: no immediate treatment (prostate-specific antigen (PSA)-based monitoring or active surveillance using PSA, MRI, biopsy with delayed treatment for disease progression) versus immediate treatment (prostatectomy or radiation therapy). Secondary outcomes include preferred management choice (from the four options listed above), diagnosis anxiety, management choice anxiety and management choice at a later time point (for participants who initially choose a monitoring strategy).

**Ethics and dissemination:**

Ethics approval has been received from The University of Sydney Human Research Ethics Committee (2023/572). The results of the study will be published in a peer-reviewed medical journal and a plain language summary of the findings will be shared on the Wiser Healthcare publications page http://www.wiserhealthcare.org.au/category/publications/https://www.wiserhealthcare.org.au/category/publications/

**Trial registration numbers:**

Australian New Zealand Clinical Trials Registry (ID 386701 and 386889).

Strengths and limitations of this studyThe randomised design will provide highly relevant evidence on the potential impacts of alternative diagnostic labels for low-risk prostate cancer on decision-making of men and women with male partners.The study has been co-designed with consumers and clinicians to ensure evidence is relevant to end-users.The two large online randomised studies will be representative of men and women with male partners in the Australian community.The hypothetical nature of the study means it cannot capture the actual experiences of patients and their partners after an actual cancer diagnosis.The study does not include male partners of men with a potential prostate cancer diagnosis. This is an important group for further research.

## Introduction

 Over the past decades, there have been large increases in the diagnosis of prostate cancer with the widespread use of prostate-specific antigen (PSA) testing.^1^,^4^ Small reductions in prostate cancer mortality (eg, decrease of 19 per 100 000 men in Australia from the peak in mid 1990s^5^) suggest this has translated into some benefit, possibly due to earlier treatment of detected aggressive cancers.^5^ However the mortality reduction is many fold smaller than the incidence increase (eg, increase of 118 per 100 000 men at Australia’s peak incidence in 2009.^6^ These and other data indicate a large proportion of detected cancers are not biologically aggressive^5 7 8^ and their detection represents overdiagnosis. Overdiagnosis refers to prostate cancer diagnoses that meet pathology diagnostic criteria, but that would not have caused symptoms or shortened the person’s life if they’d been left undetected and untreated.^9^ Overdiagnosis often leads to overtreatment with the risk of adverse effects such as erectile dysfunction and urinary incontinence.^10^,^12^ As well as overdiagnosis and overtreatment, other potential harms from PSA testing include false-positive and false-negative results, psychological stress, biopsy complications including use of and harms from, prophylactic antibiotics, labelling effect,^13^ depression,^14^ financial burden^15^ and increased social inequity in the use of healthcare resources.^16^

Avoiding immediate treatment of patients with low-risk cancers, and monitoring the patient instead, has emerged as one way to mitigate potential harms.^17^ Monitoring varies in intensity, both in testing frequency, test types used and thresholds to initiate treatment with surgery or radiation therapy. While randomised controlled trials have demonstrated comparative effectiveness of observation with additional care for symptomatic disease spread (‘watch and wait’), or active surveillance using PSA monitoring with delayed intervention with surgery or radiation,^18^,^22^ many active surveillance protocols used in practice also use periodic multiparametric MRI, biomarkers and biopsies^23^ in addition to PSA to influence treatment decisions.

Active surveillance is now widely recommended as a preferred management option, but uptake varies substantially within and between countries.^24^ This may reflect differences in clinical guideline recommendations, clinician beliefs and surveillance protocols.

Patients often lack awareness of possible options and may find it difficult to understand and weigh up potential benefits and harms to decide between them.^25^ Furthermore, individuals (and their clinicians) may perceive prostate cancer as being inevitably fatal or at least causing serious morbidity if not immediately treated. Effective strategies are needed to overcome patient and clinician barriers to choosing and adhering to conservative management (observation or active surveillance) that avoids the harms of unnecessary immediate treatment (surgery or radiotherapy). One potential strategy is to use an alternative diagnostic label that does not include the word ‘cancer’.^17 23 26^ Evidence on low-risk thyroid papillary microcarcinoma and ductal carcinoma in situ of the breast suggests that avoiding the term cancer could potentially increase the uptake of conservative management and thus improve long-term health outcomes while reducing harms.^27 28^

Two previous hypothetical randomised online experiments of prostate cancer labels have been reported. In Hudnall *et al*, 748 men without a history of prostate cancer were presented with a hypothetical scenario in which they were given a diagnosis for a low-risk prostate lesion.^29^ The men were randomised to receive one of three diagnoses using different terminology to describe the same condition: Prostate cancer Gleason Score 6 (measured on a scale from 2 to 10), versus Prostate Cancer Gleason Group 1 (measured on a scale from 1 to 5), versus indolent lesion of epithelial origin (‘IDLE’). Authors found that participants in the ‘Prostate Cancer Gleason Group 1’ label had a lower preference for immediate definitive treatment and had lower ratings of anxiety after their hypothetical diagnosis compared with the ‘Gleason Score 6’ or ‘IDLE’ labels. Berlin *et al* conducted a discrete choice experiment in three participant groups: 194 healthy men without a history of prostate cancer, 159 partners and 159 men with a history of low-risk prostate cancer (grade Group 1).^30^ Using hypothetical scenarios relating to a Gleason Group 1 prostate cancer, the authors tested different possible labels to describe pathology findings (‘adenocarcinoma’ vs ‘acinar neoplasm’ vs ‘prostatic acinar neoplasm of low malignant potential’ vs ‘prostatic acinar neoplasm of uncertain malignant potential’ (‘PAN-LMP’)), and the disease in general (‘cancer’ vs ‘neoplasm’ vs ‘tumour’ vs ‘growth’). The study found that avoiding the terms cancer and adenocarcinoma increased the likelihood of preferring active surveillance by 17%. Participants showed strong preferences for ‘tumour’ over ‘cancer’ and for ‘PAN-LMP’ over ‘adenocarcinoma’. More generally, less medicalised terms for a condition tend to be associated with less invasive management choices.^31^

The proposed study seeks to expand on this work. To ensure the relevance of our findings to end-users, we will test alternative labels for low-risk prostate cancer that were chosen by our Clinician and Consumer Co-Investigators. Alternative label(s) need to be acceptable to patients and clinicians, and convey the low, but not zero, risk of disease progression.^32^ We will undertake separate studies for men and for women who have male partners, with sufficient sample sizes to estimate label effects in both populations. We are studying women with male partners as they are often involved in deciding the preferred management of low-risk prostate cancer. Also, the diagnosis can have impacts on the female partner’s mental and physical well-being, as well as on the man receiving the diagnosis.^33 34^

This study aims to explore whether using an alternative diagnostic label to communicate a hypothetical low-risk prostate cancer diagnosis influences management choice and level of anxiety among Australian men and their partners. It further seeks to understand whether the provision of absolute risk information modifies any diagnostic label effects.^35^

## Methods and analysis

### Study structure

Two separate online randomised studies of Australian residents will be run for men and for women. For both studies, participants will be randomised to receive one of three hypothetical scenarios about the diagnosis of a low-risk prostate cancer received by themselves or their partner. Participants within each label group are then randomised to high information or low information condition, referring to the level of detail presented about the possible management options. Each group will be presented with a different diagnostic label, and we will survey participants about their preferred choice of management for that diagnosis, their level of anxiety about that diagnosis and their level of anxiety about that management choice.

The studies are structured as between-subjects factorial (3×2) online randomised experiments. The primary outcome and secondary outcomes will be compared across these randomised groups. There will be an equal probability of being assigned to each of the six groups, and we expect approximately equal numbers per group. We will use Qualtrics survey software to randomly allocate participants into groups, present the scenarios, survey questions and collect data on the outcomes (Qualtrics, Provo, Utah, USA, 2020). Our participants flow diagrams present a summary of the randomisation of participants into the allocated control and intervention arms (figures1  2).

**Figure 1 F1:**
[figure not shown]
Study Consolidated Standards of Reporting Trials flow diagram for men.

**Figure 2 F2:**
[figure not shown]
Study Consolidated Standards of Reporting Trials flow diagram for women with a male partner.

### Eligibility criteria

Two categories of participants will be eligible for the study: (1) men and (2) women. For men, participants must be 50 years or older, understand written English and be living in Australia to be included. For women, participants must have a male partner who is 50 years or older, understand written English and be living in Australia. Participants will be excluded if they, or their partner, have a history of prostate cancer.

### Recruitment and data collection

Participants will be recruited by the market research provider Qualtrics, from their pre-arranged pool of respondents who have agreed to be contacted to respond to surveys.^36^ Quotas will be used to ensure that approximately 50% of respondents are without tertiary education and the sample includes people from all Australian states and territories.

Participants who agree to participate in the study will complete an online Qualtrics survey managed by the research team. Only eligible participants will proceed to the randomisation step. The survey will capture baseline data and characteristics of participants including socio-demographic details including their age, location, health literacy and personal and family history of any cancer, personal (or partner’s) history of PSA testing and participant responses on outcome measures. The survey questions are presented in the online supplemental file 1.

All data will be collected via Qualtrics software and hosted on The University of Sydney secure server. Information will be de-identified and we will not be able to link the survey back to participants. The non-identifiable data will be downloaded for analysis and stored within The University of Sydney’s Research Data Store.

### Intervention

Participants will be randomised using Qualtrics randomisation software to receive one of three hypothetical scenarios. They will not be blinded. In each scenario, the participant will be told they have received a particular diagnosis. Group 1 (the control group) will be told they have a ‘low-risk prostate cancer, Gleason Group 1’. The alternative labels for Groups 2 and 3 were chosen by Consumer and Clinician Co-Investigators (see section v. Determination of alternative labels to be tested). Group 2 will be told they have a ‘low-risk prostate neoplasm’, and Group 3 will be told they have a ‘low-risk prostate lesion’.

Within each scenario arm, participants will be further randomised to receive either limited information about their diagnosis and management options (a short description of the diagnosis and the management options available, see box 1) or more comprehensive information about their diagnosis and management options (additionally including the absolute rates of problems with erectile, urinary and bowel function and of metastatic spread, as reported in the two randomised controlled trials (RCTs) that included a majority with PSA-detected cancer: the PIVOT^18^,^20^ and ProtecT RCTs^12 21 22^ (see figure 3).

Box 1Explanation of management options for men (equivalent text used for women with male partners)Prostate-specific antigen (PSA) monitoring, where you keep visiting the doctor to get check-ups and tests. You will be monitored at regular points in time with PSA blood tests. This is to monitor the way the (diagnostic label) behaves. If it shows signs of growing, then treatment can be started.Active surveillance, where you keep visiting the doctor to get check-ups and tests. Your will be monitored at regular points in time with PSA blood tests, MRI scans and prostate biopsies. This is to monitor the way (diagnostic label) behaves. If it shows signs of growing, then treatment can be started.Prostatectomy, where you have a surgical procedure to remove the prostate. This includes the (diagnostic label).Radiotherapy, where you have a non-surgical procedure on the prostate. The prostate is treated with radiation to destroy the (diagnostic label).Studies have reported the health outcomes for men diagnosed with low-risk prostate cancer, grade Group 1 who had one of these options. The studies found that for every 100 men found to have low-risk prostate cancer, grade Group 1, 2 men will die because of their condition over the next 15 years, regardless of the treatment that is given. Different ways of managing the condition have advantages and disadvantages.

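### Box 1 hard-codes the cancer wording in text that, as printed, goes to every label arm, which probably dilutes the label contrast on management choice

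*Protocol article*

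**What the plan says.** The Intervention section of the Protocol article assigns three labels. The control arm's label contains the word 'cancer' and ends in 'Gleason Group 1'. For the other two, "Group 2 will be told they have a ‘low-risk prostate neoplasm’, and Group 3 will be told they have a ‘low-risk prostate lesion".

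Within each label arm, participants are randomised again. Half receive "limited information about their diagnosis and management options (a short description of the diagnosis and the management options available, see box 1". The other half receive fuller information, "additionally including the absolute rates of problems with erectile, urinary and bowel function and of metastatic spread".

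Box 1 is headed as the text for men, with "equivalent text used for women with male partners". Its four option descriptions each carry a placeholder, for example "This is to monitor the way the (diagnostic label) behaves". The closing paragraph has no placeholder. It says "Studies have reported the health outcomes for men diagnosed with low-risk prostate cancer, grade Group 1 who had one of these options". It then gives the mortality figure, counted in years: "for every 100 men found to have low-risk prostate cancer, grade Group 1, 2 men will die because of their condition over the next 15".

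**The concern.** The Introduction presents the strategy under study as a diagnostic label that leaves out the word 'cancer'. The label is the randomised factor, and the primary outcome is the choice between no immediate and immediate treatment. If the text explaining the options tells the neoplasm and lesion arms that those options were studied in men with prostate cancer, and that a stated share of those men die of their condition, readers in those arms can easily conclude that their own finding is cancer. The three arms then differ less than the design intends.

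The likely result is a smaller difference in management choice, and possibly in management-choice anxiety. A null finding would be hard to interpret: it could mean that labels do not matter, or that the shared text undid the label.

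A smaller point lies in the same sentences. Box 1 writes 'grade Group 1' where the Abstract and the Intervention section give the control label as 'Gleason Group 1', so even the control arm meets two versions of its label.

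**Working it through.** **Who reads the fixed text**

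1. The limited-information condition receives Box 1 within each label arm (Intervention).
2. The fuller condition is described as receiving further content in addition. It therefore also receives the Box 1 content.
3. Three labels × two information levels = six cells. As printed, all six receive the closing paragraph, and four of the six carry a non-cancer label. The same holds for the women's study if its equivalent text follows Box 1.

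**Is the fixed text just the control arm's version?**

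- The placeholder appears four times in the box, once per option. A printed control version would have had these filled in.
- The fixed phrase appears twice and does not match the control label ('grade' against 'Gleason').
- The box is headed as the text for men, not for one arm.

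Nothing in the article says that this paragraph varies by arm.

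**Illustration of size**

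Inputs from the Sample size and Analysis sections: control proportions 70% (men) and 65% (women); a 10-point difference; 430 and 470 per label group; 5% dropout; two-sided α = 0.05. Evaluable n per group is 0.95 × 430 = 408.5 and 0.95 × 470 = 446.5. The effect is taken as an increase from the control rate.

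The plan's own figure comes first. The same normal-approximation formula at 80% power gives 294 per group for 70% vs 80%, and 294/0.95 rounds up to 310. For 65% vs 75% it gives 329, and 329/0.95 rounds up to 347. The stated 430 and 470 are larger and are not reproduced from the stated inputs. That is a separate matter, and the present point does not depend on it. It does explain why the undiluted power below exceeds 80%.

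Power = Φ{ [d√n − 1.96·√(2p̄(1−p̄))] / √(p₁(1−p₁) + p₂(1−p₂)) }, where p̄ is the mean of p₁ and p₂.

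- Men, d = 0.10: (2.0211 − 1.2002)/0.6083 = 1.350, power 91%.
- Men, d = 0.075: (1.5159 − 1.2196)/0.6200 = 0.478, power 68%.
- Men, d = 0.05: (1.0106 − 1.2377)/0.6305 = −0.360, power 36%.
- Women, d = 0.10: (2.1131 − 1.2702)/0.6442 = 1.308, power 90%.
- Women, d = 0.075: (1.5848 − 1.2848)/0.6534 = 0.459, power 68%.
- Women, d = 0.05: (1.0565 − 1.2982)/0.6614 = −0.365, power 36%.

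The shrinkage of 0%, 25% and 50% is assumed. The document gives no figure for it.

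**The case against.** The strongest reply is that Box 1 is a print template, not the survey. The survey questions are in a supplemental file that is not shown, and the live version may substitute the label throughout. This stands as a limit: a reader might infer that the primary contrast has been shown to be contaminated, and the document does not support that. What it supports is a conditional statement about the text as printed. The unseen supplement cannot be assumed to repair that text, and if the survey does substitute the label, the article misdescribes its intervention.

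The order of screens is also not given. A reader might infer that participants meet the cancer wording immediately before choosing, or that every anxiety outcome is affected. The first is only plausible, because the box explains the options to be chosen from. On the second, diagnosis anxiety is exposed only if it is asked after Box 1.

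It can also be said that cancer-free exposure was never intended, since all arms answer questions on cancer history and cancer worry and are screened for prostate cancer. That is weaker. Such questions do not tie the participant's hypothetical diagnosis and options to cancer, whereas the closing paragraph does.

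Naming the studied population may have been deliberate, to report the source trials faithfully. Putting a new label on those trial populations does carry a cost in accuracy, and neutral wording reduces it.

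The 'grade'/'Gleason' mismatch is not decisive alone, because the Introduction uses both terms for the same condition.

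Finally, randomisation remains valid. The comparison still estimates the effect of the assigned label, given the shared text.

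**Conclusion.** The point holds for the intervention text as printed. Box 1 varies the label in its option descriptions and then fixes the cancer wording twice, in text assigned to every arm at both information levels. This conflicts with testing labels that avoid the word 'cancer'.

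The probable consequence is dilution of the label effect on management choice and possibly on management-choice anxiety. The direction is likely rather than certain, and the size cannot be derived from the document. The power range of about 91%/90% down to 36%/36% shows only how sensitive the trial would be to a shrinkage between none and one half. It rests on the planned control rates, 5% dropout and unadjusted two-sided tests at 5%.

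The point must be resolved because it decides what the primary comparison estimates and how a null result may be read.

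**What to change.** 1. Check the deployed survey text for Groups 2 and 3 in both studies, and state which wording they saw and where it came relative to each outcome question.
2. If the text can still be changed, replace both fixed phrases in the men's and women's versions with the label placeholder or with neutral wording such as 'your condition' (adapted for partners). Neutral wording avoids attributing a new label to the trial populations. Edit Figure 3 only if it contains the same phrase.
3. Use one wording of the control label throughout.
4. If data were collected with the fixed text, state that the trial estimates the label effect given shared disclosure of the cancer term, and that a null result cannot be read as no effect of avoiding the word 'cancer'.
5. If the survey substituted the label, correct the printed Box 1.

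The change is a small text edit and adds no participants. The article anticipated that data collection would end on 30 April 2024, so items 4 or 5 may be the only ones available. The Ethics and dissemination section already provides for versioned protocol updates. It does not say what ethics step a wording change would need.

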**Figure 3 F3:**
[figure not shown]
Additional information on absolute benefits and harms of management options provided in high information condition.^1^ Risk estimates are based on long-term follow-up in the PIVOT^18^,^20^ and ProtecT randomised controlled trials.^12 21 22^ PSA, prostate-specific antigen.

